#### Dropout

Participants can voluntarily withdraw at any time during the trial. Participants who meet the inclusion criteria, provide a completed and signed consent form, and successfully enter the randomized trial but fail to complete the proposed observational period, regardless of time and reason, will be regarded as dropout cases. Dropout cases include:Poor treatment compliance (< 80%), use of forbidden medicines, or change in treatment without consent from the study supervisor.Voluntary withdrawal or incomplete clinical data, affecting the evaluation of efficacy and safety.Occurrence of serious AEs or complications, resulting in the discontinuation and unblinding of the treatment.

### Interventions

Patients in the LSXG group will receive the umbilical therapy with LSXG cataplasm plus red light irradiation along with conventional treatment, whereas patients in the placebo group will receive the placebo cataplasm plus red light irradiation along with conventional treatment. The treatment will be administered once daily for up to 10 days, with a 30-day follow-up after the last treatment.

#### Traditional Chinese medicine intervention

The LSXG cataplasm comprises Pharbitidis Semen (Qianniuzi) 15 g, Plantaginis Semen (Cheqianzi) 9 g, *Rheum officinale* (Dahuang) 9 g, Coicis Semen (Yiyiren) 9 g, Costustoot (Muxiang) 6 g, and Kansui Radix (Gansui) 6 g. The composition of specific Chinese herbal remedies and their actions are summarized in Table 1 [11]. Placebo cataplasm comprises 1% of the formulation mentioned and 99% dextrin and caramel. It resembles the LSXG formula in appearance, color, and scent. Both cataplasms are manufactured and quality controlled by Beijing Tcmages Pharmaceutical Co., Ltd. (Beijing, China) according to industry standards. All of the drugs are uniformly packaged and identified with the same labels.

**Table 1 Tab1:** Composition and effects of herbs in the *Lishui Xiaogu* cataplasm

Ingredient	Pharmacological effects according to traditional Chinese medicine
Qianniuzi	Purging water and relieving constipation, clearing away phlegm and expelling water, killing worms, and resolving accumulation
Cheqianzi	Clearing heat, diuresis and treating stranguria, dispelling dampness to stop diarrhea, improving vision, and dispelling phlegm
Dahuang	Contributing to defecation to resolve accumulation, clearing heat and purging fire, cooling blood to remove toxins, removing blood stasis and promoting menstruation, dispersing dampness, and eliminating jaundice
Yiyiren	Eliminating dampness and disinhibiting water, strengthening the spleen to stop diarrhea, removing obstruction, expelling pus, detoxicating, and resolving stasis
Muxiang	Regulating qi to stop pain, and invigorating the spleen to promote digestion
Gansui	Removing retained water and morbid fluid, subduing swelling, and dissipating bind

Administration method: 0.5 g of the formula will be combined with rice wine to form a paste, which will be applied to the patient’s umbilical region for 120 min and then exposed to red light for 20 min once a day.

For cataplasm application: the umbilical region should be thoroughly cleaned with an iodophor solution; the patients must be rested and abstain from stimulating food, such as pungent food, seafood, or raw and cold food, and the cataplasm should not be applied immediately before a meal; the amount of formula administered and the time of administration should be adjusted for weaker patients (any changes in patient conditions should be recorded); if the cataplasm application triggers erythema, blisters, or itching, it should be removed; and the cataplasm should be contraindicated in patients with known allergies to any of the constituents, pregnant patients, and patients presenting with edema with Yin-shui syndrome. This application should be used with caution in weaker patients.

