### Ethics

The study protocol has been approved by the Institutional Review Board of Dongzhimen Hospital, affiliated to the Beijing University of Chinese Medicine (No. ECPJ-BDY-2015-69), and has been registered with the Chinese Clinical Trial Registry (ChiCTR-INR-16007686). The Institutional Review Board will be responsible for supervising all procedures of the study, including patient recruitment, randomization, treatment administration, data storage, and so on. In the case of any changes to the original study protocol, a written application will be submitted to the Institutional Review Board for approval. The study will be conducted according to the Good Clinical Practice Guidelines and the principles of the Declaration of Helsinki. Results will be reported according to the same guidelines.

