### Randomization and allocation concealment

The randomization sequence will be generated using SAS software, version 9.4 (SAS Institute). The central randomization system used in this trial was provided by the Institute of Basic Research in Clinical Medicine, China Academy of Chinese Medical Sciences. It is an online platform. Each center staff member logs into the website when the participant is enrolled, enters the basic information of the participant, and then obtains a random number. Eligible participants will be randomly assigned to the LSXG or the placebo group in a ratio of 1:1. All eligible participants will obtain the corresponding umbilical drug according to their random number, and they will be individually treated to prevent communication. The participants, researchers, and statisticians will be blinded to treatment allocation.

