### Inclusion criteria

Participants who meet the following criteria will be included in the study:Presence of grade 2–3 ascites according to the diagnostic standards of liver cirrhosis [5]: cirrhosis patients with symmetrical distension of the abdomen, and ascites depth > 3 cm.Age between 18 and 75 years, irrespective of sex.An agreement to voluntary participation in the trial and the provision of informed consent.

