### Exclusion criteria

Participants who meet any of the following criteria will be excluded:Presence of liver cirrhosis decompensation accompanied by bleeding, gastrointestinal hemorrhage, hepatic encephalopathy, hepatorenal syndrome, and other serious complications.Presence of a combination of severe cardiovascular, lung, kidney, neuronal, and blood circulation system diseases as well as other serious illnesses, such as mental illness, or tumors.Current or planned pregnancy, or nursing mothers.Presence of allergic constitution, or a past medical history of allergies to umbilical drugs or their known components.Participation in other clinical trials within 1 month before our study.

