### Exclusion criteria

#### Rejection

Participants who meet any of the following exclusion criteria will be rejected:Not following the inclusion criteria.Dropout during the observation period, without any data recorded.Discontinuation of treatment following the baseline time.

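### Edema with Yin-shui syndrome is a stated contraindication to the cataplasm but not an exclusion criterion; the albumin unit and the lowest spironolactone dose also need correction

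*Protocol article*

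**What the plan says.** **Contraindications.** In the Protocol article, the application instructions under Traditional Chinese medicine intervention name three groups who should not receive the cataplasm: people with a known allergy to a constituent, and "pregnant patients, and patients presenting with edema with Yin-shui syndrome".

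**Eligibility.** The Exclusion criteria list "Current or planned pregnancy, or nursing mothers" and "Presence of allergic constitution, or a past medical history of allergies to umbilical drugs or their known components". They do not mention Yin-shui edema. The Inclusion criteria ask for grade 2–3 ascites, described as "cirrhosis patients with symmetrical distension of the abdomen" with a depth above 3 cm, plus age 18 to 75 and consent. They set no restriction by syndrome.

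**Blinding.** Under Randomization and allocation concealment: "The participants, researchers, and statisticians will be blinded to treatment allocation". The placebo cataplasm contains 1% of the active formulation.

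**Patients who stop.** Informed consent keeps the data of people who withdraw for the final analyses. Discontinuation includes the last recorded data of people who stop treatment. Statistical analysis promises intention-to-treat for the primary outcome.

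**Background treatment.** Conventional treatment gives spironolactone 40–100 mg/day with furosemide 20–40 mg/day at 5:2, and albumin infusion when serum albumin is below 25 g/dl.

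**The concern.** A contraindication that can be recognised when the patient presents belongs among the entry criteria, so that it acts before randomisation. Two of the three stated contraindications do sit there and the third does not. The article prints both lists item by item and they disagree on one item, so this is an inconsistency on the page rather than a detail left to a fuller document.

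What is at stake is mainly patient safety. Site staff who work from the eligibility lists alone would accept a patient whom the application instructions say must not be treated. Because staff are blinded and the placebo contains some of the formula, the question would arise in either arm.

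The two rules under Conventional treatment matter less. They govern diuretics and albumin, which bear on ascites and so on the primary outcome, and neither can be followed exactly as printed.

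**Working it through.** **1. Contraindications set against the entry rules**

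| Contraindication | In Exclusion criteria? |
|---|---|
| Allergy to a constituent | Yes: "Presence of allergic constitution, or a past medical history of allergies to umbilical drugs or their known components" |
| Pregnancy | Yes: "Current or planned pregnancy, or nursing mothers" |
| Edema with Yin-shui syndrome | No |

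Two of three are carried over. The remaining rules do not supply the third:

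- Inclusion criteria: a patient with Yin-shui edema can meet every item.
- Rejection: this removes people who fail the inclusion criteria, which such a patient need not do.
- Discontinuation and Dropout: these concern what happens after entry.
- The catch-all wording in the Exclusion criteria about serious complications and illnesses follows lists of organ-level events and diseases. It does not clearly reach a syndrome pattern of traditional Chinese medicine, and the application instructions name that pattern separately.

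**2. Dose if the contraindication were missed**

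Each application uses 0.5 g of the formula. Assuming the same weight of placebo paste powder, the placebo arm would receive 0.5 g × 1% = 0.005 g.

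**3. How many patients a new criterion could still screen**

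The planned total is 82, and Trial status reports 78 enrolled at submission. 82 − 78 = 4, and 4/82 = 4.9%. The frequency of Yin-shui edema is not given, so the number of affected patients among the 78 cannot be computed.

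**4. Albumin threshold**

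1 g/dl = 10 g/L, so 25 g/dl = 25 × 10 = 250 g/L. No patient's serum albumin reaches that level, so the printed rule selects everyone. If 25 g/L is meant, the equivalent is 25/10 = 2.5 g/dl.

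**5. Diuretic rule**

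The plan's ratio is 5:2 = 2.5.

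- Upper ends: 100/40 = 2.5, which agrees.
- Lower ends: 40/20 = 2.0, which does not.
- For a spironolactone dose S, the ratio requires furosemide of 2S/5. At S = 40 this is 40 × 2/5 = 16 mg, below the 20 mg minimum.
- The minimum is met when 2S/5 ≥ 20, that is, S ≥ 20 × 5/2 = 50 mg.

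The rule therefore works from 50 to 100 mg/day and fails from 40 to just under 50 mg/day. That is 10 mg of a 60 mg range. It is an interval of doses and says nothing about what share of patients receives them.

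The sample size of 41 per group does not depend on any of these points.

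**The case against.** The strongest reply is that the safeguard is already in the protocol. The application instructions forbid the cataplasm in these patients, so exposure would require a breach. They set no time at which the check is made, and nothing prevents staff from recognising the syndrome and declining to enrol. This stands, and it limits the point: a safety restriction is misplaced, but no unsafe instruction is given. It does not remove the inconsistency, because the list that decides entry still admits the patient.

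A reader might infer four stronger things that the documents do not support:

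- **That staff are bound to withhold treatment after allocation, diluting the effect.** The text does not fix the timing. The number of such patients is unknown, so any dilution figure would rest on an invented count.
- **That the trial cannot identify these patients.** The baseline list names symptoms and no syndrome item, but it is given by way of example and ends with an open category for other information. An item not named in a condensed list may still be collected.
- **That the analysis of these patients is left unsettled.** Rejection does list "Discontinuation of treatment following the baseline time", and Dropout counts "Poor treatment compliance (< 80"%). However, Informed consent, Discontinuation and Statistical analysis all lean towards keeping the data. The tension that remains applies to anyone who stops treatment and is not particular to Yin-shui edema.
- **That the comparison is biased.** Allocation is blinded, and the gap in eligibility is the same for both arms.

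On the two treatment rules, it is fair to say that the albumin figure is an evident unit slip that no clinician would apply literally, and that the diuretic conflict touches only the lowest doses. Both are errata, but they sit in operative treatment instructions and should be right.

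**Conclusion.** The point holds as a mismatch between the stated contraindications and the eligibility rules: a patient with Yin-shui edema is eligible as written for a product that the protocol contraindicates. It is worth correcting for safety and costs little. Its reach is small. At most 4 of the planned 82 patients (4.9%) could still be screened, counting from the 78 reported at submission. The number already affected is unknown, and neither between-arm bias nor a loss of power is shown.

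This rests on reading the printed exclusion list as complete, and on the view that its general wording does not extend to a syndrome pattern.

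The albumin threshold and the lower spironolactone bound are wrong as printed. They apply equally to both arms and change no estimate, test or sample size. Reading the albumin unit as g/L is a presumption for the sponsor to confirm.

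**What to change.** 1. Add edema with Yin-shui syndrome to the Exclusion criteria, and check it before randomisation for the patients still to be enrolled.
2. State that any such patient already randomised stays in the intention-to-treat analysis, in line with Informed consent, Discontinuation and Statistical analysis.
3. Correct the albumin threshold, presumably to 25 g/L (2.5 g/dl), once the sponsor confirms it.
4. Start the spironolactone range at 50 mg/day, which gives 50:20 and 100:40, both exactly 5:2. Stating that the ratio does not bind at the lowest dose would also remove the conflict.

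The cost is one added criterion, one sentence on analysis and two text corrections. The Ethics section already sets the route for the added criterion: "In the case of any changes to the original study protocol, a written application will be submitted to the Institutional Review Board for approval". The sample size does not change.

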#### Conventional treatment

Following the available clinical guidelines [12, 13], the patients will be provided with conventional general treatment, including rest, limited salt intake (approximately 60–90 mmol of sodium per day), and limited water intake, and etiological treatment, including diuretics (spironolactone (40–100 mg/day) and furosemide (20–40 mg/day), at a ratio of 5:2), liver protection treatment (including reduced glutathione, polyene phosphatidyl choline, tiopronin, silibinin, etc.), and albumin infusion for patients with serum albumin levels of < 25 g/dl.

### Sample size

In our previous study, the estimated total effective size of the study population was 87.5% for TCM application and 62.5% for the control treatment [14]. At *α* = 0.05 and *β* = 0.20, and assuming a dropout rate of 10%, the one-tailed test provided an estimated sample size of 41 patients per group.

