### Primary outcomes

The primary outcome measurement will be the depth of ascites. It will be measured at baseline using B-ultrasound, after the intervention (10 days), and at the end of the 30-day follow-up period.

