### Statistical analysis

The data from all participating centers will be combined for statistical analysis of the primary and secondary outcomes as well as the AEs. The statistical analysis will be performed at the Institute of Basic Research in Clinical Medicine, China Academy of Chinese Medical Sciences. The primary outcome will be analyzed according to the intention-to-treat principle. To compare the difference between two groups, independent *t* tests (or the Mann–Whitney *U* test) will be used to analyze continuous data and the chi-squared or Fisher’s exact test will be used for categorical data. Repeated-measures ANOVA will be used to account for the time effect.

For all measures, two-sided *p* < 0.05 will be considered statistically significant. Statistical analyses will be performed using SAS software version 9.4 (SAS Institute, Cary, NC, USA).

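### The sample size and its 80% power rest on a binary total-effective rate that is not a trial outcome, so they do not apply to ascites depth and cannot be verified for it

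*Protocol article*

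**What the plan says.** The Sample size section of the protocol article relies on two percentages from an earlier study: "the estimated total effective size of the study population was 87.5% for TCM application and 62.5% for the control treatment". With α = 0.05 and β = 0.20 it continues: "and assuming a dropout rate of 10%, the one-tailed test provided an estimated sample size of 41 patients per group".

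The Primary outcomes section names a measurement: "The primary outcome measurement will be the depth of ascites". It is taken by B-ultrasound at baseline, after the 10-day intervention and at the end of the 30-day follow-up. The Inclusion criteria give its unit, with an entry threshold above 3 cm. The Secondary outcomes section lists abdominal perimeter, body weight, 24-hour urine volume, the TCM symptom score and the CLDQ. The Abstract and the Study design section give the same lists.

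The Statistical analysis section assigns methods by data type. t tests or the Mann–Whitney test "will be used to analyze continuous data", chi-squared or Fisher's exact tests are for categorical data, and repeated-measures ANOVA is for the time effect. The significance level is set with the words "For all measures, two-sided" p < 0.05.

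**The concern.** The sample size compares two proportions of patients counted as effectively treated. The article lists no such outcome, gives no responder threshold, and has no rule that turns a depth in cm into effective or not effective. It also gives no target difference and no SD for depth.

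At stake is how the result will be read. If depth shows no significant difference, a reader of the Sample size section will assume the trial had 80% power to find a relevant one. The article does not say how large a difference in depth it could detect, so that reading has no basis. In addition, an undefined effective rate that supports the sample size could later look pre-planned if it were reported. Nothing in the article proposes to report one, so this second point is a precaution only.

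**Working it through.** **Inputs from the article.** Rates 0.875 and 0.625; α = 0.05, one-tailed; power 0.80; dropout 10%; 41 per group (Sample size). Two-sided 0.05 for the analysis (Statistical analysis).

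**Step 1: reproduce the stated figure.** Two proportions, pooled variance under the null, no continuity correction, with mean rate p̄ = (0.875 + 0.625)/2 = 0.75:

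n = [z(0.95)·√(2·p̄·(1 − p̄)) + z(0.80)·√(p1(1 − p1) + p2(1 − p2))]² / (p1 − p2)²

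- First term: 1.645 × √0.375 = 1.645 × 0.6124 = 1.007
- Second term: 0.842 × √(0.1094 + 0.2344) = 0.842 × 0.5863 = 0.493
- n = (1.007 + 0.493)² / 0.25² = 36.03, so 37 per group
- Dropout: 37 × 1.1 = 40.7, so 41, the stated figure. Dividing instead, 37/0.9 = 41.1, gives 42.

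The arithmetic is sound on its own inputs. It also confirms that the 41 comes from a binary comparison.

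**Step 2: look for that endpoint.** The Abstract, Study design, Primary outcomes and Secondary outcomes sections contain no effective rate. No section gives a cut-off on depth.

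**Step 3: what the same numbers give for depth.** No SD is stated, so results are in SD units (d = difference in means divided by SD). The calculation is for an unadjusted two-sample t test at one time point, two-sided 0.05. Power comes from the noncentral t distribution with 2n − 2 degrees of freedom and noncentrality d·√(n/2). Evaluable per group: 41 × 0.9 = 36.9, taken as 37.

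| | 37 per group | 41 per group |
|---|---|---|
| d with 80% power | 0.660 | 0.626 |
| Power at d = 0.3 | 25% | 27% |
| Power at d = 0.4 | 40% | 43% |
| Power at d = 0.5 | 56% | 61% |

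**Step 4: what a link would give if there were one.** Suppose, as an assumption only, that total effective in the earlier study was a cut-off on ascites depth, with normal distributions of equal variance. Then d = z(0.875) − z(0.625) = 1.150 − 0.319 = 0.83. Two-sided t-test power would be about 94% with 37 per group and 96% with 41. Nothing in the article says that the rate was defined this way.

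**Step 5: sensitivity to the analysis.** If depth were adjusted for baseline, the effective standardised difference would be d/√(1 − ρ²), where ρ is the correlation between baseline and follow-up depth. With assumed ρ of 0.5 to 0.7, d = 0.5 becomes 0.5/0.866 = 0.58 to 0.5/0.714 = 0.70. Power with 37 per group is then about 69% to 84%. The article does not specify such an adjustment.

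**The case against.** The strongest reply is that the rate and depth may be connected. The Discussion says the trial builds on the earlier study in the same sentence that names change in ascites on ultrasound as the primary outcome. If the effective rate was a cut of depth, Step 4 shows that power for depth could exceed 90%. This stands as far as it goes. A reader might infer from the mismatch that the stated power has no bearing at all on depth, or that the trial is underpowered. The article supports neither, because the earlier study's definition is not shown. The same gap prevents the reply from rescuing the power statement: a link that is not stated cannot be checked.

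A second reply is that the analysis of depth is not tied down. Methods are assigned by data type, and repeated-measures ANOVA is also named. That depth is analysed as continuous is an inference from its cm scale, the absence of any cut-off and the methods listed. It is the only reading with support in the text. The reply does limit Step 3: the 0.66 SD figure describes one unadjusted comparison and should not be presented as the sensitivity of every possible analysis.

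Third, recruitment is nearly complete (78 of 82), and estimates and p-values for depth stay valid whatever the sample size rationale. That is correct, and it is why the remedy is a restatement and not a redesign. A separate analysis plan could add a calculation for depth, but the article's own complete power statement would still be for another endpoint.

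**Conclusion.** The concern holds in this form: 41 per group and 80% power come from a one-sided comparison of a binary rate that is neither a primary nor a secondary outcome. With no stated link to depth, and no target difference or SD for depth, the power claim does not apply to the primary outcome and cannot be verified for it.

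On size: at two-sided 0.05, an unadjusted comparison of mean depth at one time point has 80% power for about 0.66 SD with 37 evaluable per group, or 0.63 SD with all 41. Whether that is a realistic or clinically relevant difference cannot be judged without an SD and a target in cm.

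This rests on depth being analysed as continuous, on equal variances and approximate normality, and on 10% loss. It is a fault in the stated justification, and it does not invalidate the comparison of depth itself.

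**What to change.** Restate the Sample size section for ascites depth at the two-sided 0.05 level used in the Statistical analysis section. Suggested content: with 41 per group and 10% loss (37 evaluable), an unadjusted comparison of mean depth at one named time point has 80% power for a difference of about 0.66 SD (0.63 SD with no loss), and 56% to 61% power at 0.5 SD. Present this as the sensitivity of a sample already fixed, not as proof that 0.66 SD is clinically relevant.

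Convert to cm only with an SD of post-treatment depth or of change in depth, from the earlier study or from blinded pooled day-10 data. The baseline SD is unsuitable: baseline depth is truncated by the entry rule of more than 3 cm, and its spread is that of neither post-treatment depth nor change.

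Say that the total-effective rate was the historical basis for the number. Then either state that it will not be used as evidence of efficacy, or define it as a secondary outcome before unblinding.

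The cost is rewording and, if the earlier study gives no usable SD, one blinded SD calculation. No extra patients are needed. The downside is a less favourable stated sensitivity.

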**Methods/design:**

This ongoing study is a double-blind, randomized, parallel, placebo-controlled trial. A total of 82 patients will be recruited and randomly assigned to either a treatment group or a placebo group, in a 1:1 ratio. The treatment group will receive umbilical therapy with the *Lishui Xiaogu* cataplasm plus red light irradiation along with conventional treatment; the placebo group will receive umbilical therapy with a placebo cataplasm plus red light irradiation along with conventional treatment. Interventions for both groups will be administered once daily for up to 10 days, with a 30-day follow-up after the last treatment. The primary efficacy measurement will be ascites depth. Secondary efficacy measurements will include abdominal perimeter, weight, urine volume, the symptomatic score of traditional Chinese medicine, and the Chronic Liver Disease Questionnaire. Adverse events will also be reported.

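### The trial is sized for a one-tailed test at 0.05 but will be analysed two-sided at 0.05, so on its own assumptions power is about 71%, not the stated 80%

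*Protocol article*

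**What the plan says.** The Sample size section of the protocol article takes its effect from an earlier study by the same group, in which the effective rate "was 87.5% for TCM application and 62.5% for the control treatment". It sets alpha at 0.05 and beta at 0.20 (80% power), allows for 10% dropout, and concludes that "the one-tailed test provided an estimated sample size of 41 patients per group". The abstract carries this forward: "A total of 82 patients will be recruited and randomly assigned to either a treatment group or a placebo group, in a 1:1 ratio".

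The Statistical analysis section sets a different rule for significance: "For all measures, two-sided *p* < 0.05 will be considered statistically significant". That covers every outcome, including the primary one. The article gives no reason for the difference and describes no one-sided analysis anywhere.

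**The concern.** A one-tailed test at 0.05 rejects beyond a critical value of 1.645. A two-sided test at 0.05 rejects beyond 1.960. If the number of patients was derived with the first and the data are judged by the second, the sample size does not pay for the stricter threshold, and the stated type II error of 20% does not belong to the test that will be run.

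Two things are at stake. First, a null result could be read as coming from a trial with 80% power when its power, on the assumptions given, is lower. Second, two conflicting statements on sidedness leave some room to invoke the one-tailed test once the data are known. That would double the false-positive rate in the favourable direction from 2.5% to 5%.

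**Working it through.** **Inputs, all from the protocol article**

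- p1 = 0.875, p2 = 0.625, so the difference d = 0.25 and the mean rate is 0.75 (Sample size)
- alpha 0.05, beta 0.20, dropout 10%, one-tailed, 41 per group (Sample size)
- two-sided 0.05 for all measures (Statistical analysis)
- 82 patients, 1:1 (Abstract)

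**Formula** (two proportions, pooled variance under the null, no continuity correction)

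n per group = [z_α √(2 × 0.75 × 0.25) + z_β √(p1(1−p1) + p2(1−p2))]² / d²

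The two square roots are √0.375 = 0.6124 and √(0.1094 + 0.2344) = √0.3438 = 0.5863. With z_β = 0.8416 the second term is 0.4934, and d² = 0.0625.

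**Step 1. Reproduce the stated figure, one-sided**

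n = (1.6449 × 0.6124 + 0.4934)² / 0.0625 = (1.5007)² / 0.0625 = 36.03

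36.03 / 0.9 = 40.04, rounded up to 41. Rounding to 37 first and multiplying by 1.1 gives 40.7, again 41; dividing 37 by 0.9 gives 42. The stated 41 is reproduced.

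**Step 2. The same calculation, two-sided**

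n = (1.9600 × 0.6124 + 0.4934)² / 0.0625 = (1.6937)² / 0.0625 = 45.9, so 46 evaluable per group

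With dropout: 46 × 1.1 = 50.6, so 51; 46 / 0.9 = 51.1, so 52. The total is 102 to 104, against 82.

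The choice of formula does not explain the gap. Across the unpooled, arcsine, common-variance and continuity-corrected versions, the two-sided requirement with dropout runs from 49 to 60 per group, never 41.

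**Step 3. Power of the planned size**

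Power = Φ{[d√n − z_α × 0.6124] / 0.5863}. Evaluable per group after 10% loss: 41 × 0.9 = 36.9, taken as 37.

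For 37, two-sided: (0.25 × 6.083 − 1.2002) / 0.5863 = 0.547, and Φ(0.547) = 0.708.

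For 41, two-sided: (0.25 × 6.403 − 1.2002) / 0.5863 = 0.683, and Φ(0.683) = 0.753.

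| Evaluable per group | One-sided 0.05 | Two-sided 0.05 |
|---|---|---|
| 37 (10% lost) | 80.9% | 70.8% |
| 41 (none lost) | 84.4% | 75.3% |

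**Step 4. Sensitivity of the two-sided power**

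| Method | 37 per group | 41 per group |
|---|---|---|
| Pooled normal (as above) | 70.8% | 75.3% |
| Arcsine | 72.6% | 76.9% |
| Unpooled normal | 73.7% | 78.0% |
| Chi-squared, exact enumeration | 72.0% | 76.8% |
| Fisher's exact test, exact enumeration | 63.1% | 69.1% |

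None reaches 80%. Fisher's test is named as an alternative in the Statistical analysis section, but the expected number of non-responders per arm is about 9 (37 × 0.25 = 9.25), so chi-squared would ordinarily apply. The Fisher row is a lower bound and the conclusion does not rest on it.

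**The case against.** The strongest objection is that 71% is not the power of this trial's primary analysis. The Primary outcomes section says "The primary outcome measurement will be the depth of ascites", a continuous measure to be compared by t test or Mann–Whitney test with repeated-measures ANOVA, and the effective rate used for sizing is not among the listed outcomes. This stands as a limit on what the 71% means. The article gives neither a difference nor a standard deviation for depth, so its power could be higher or lower and cannot be computed. It does not rescue the Sample size section, however. The effective rate is the only basis offered for the 80% claim, and on that basis the claim fails under the declared test. The mismatch of outcomes is a separate matter.

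Second, the primary analysis is by intention to treat, and the last recorded data of discontinued participants are to be used, so part of the 10% may still be analysed. On the other hand, the Rejection paragraph removes some participants. The evaluable number therefore lies somewhere between 37 and 41, and 71% to 75% is the fair range.

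Third, the Statistical analysis section already fixes the stricter rule, and the one-tailed test is mentioned only for sizing. That is largely right: read literally, the type I error is controlled and a positive two-sided result is not undermined. The risk of a later switch is secondary to the misstated power.

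Fourth, there is no slip in the arithmetic, since 41 follows from the one-tailed assumption, which is openly stated. True: the fault is an inconsistency between two sections, and its consequence is numerical.

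**Conclusion.** The concern holds. The Sample size and Statistical analysis sections contradict each other on sidedness, and the figure of 41 per group rests on the one-tailed version. Under the two-sided test that will be used, the type II error rises from the stated 20% to about 29% with the planned dropout (100 − 70.8), or about 25% with no loss (100 − 75.3). Two-sided 80% power would need about 10 to 11 more patients per group (51 to 52 against 41).

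This rests on the protocol's own rates of 87.5% and 62.5%, its 10% dropout, and the pooled formula that reproduces its 41. It applies to the binary effective rate only.

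**What to change.** Keep the two-sided 0.05 criterion and the 82 patients. Correct the Sample size section to say that 41 per group was derived for a one-tailed test, and that under the two-sided test in the Statistical analysis section it gives about 71% power for 87.5% versus 62.5% with 10% dropout, or 75% with no loss. State that these figures refer to the effective rate used for sizing and not to ascites depth. Add that no one-tailed result will be used to claim efficacy.

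The cost is a short text correction and a less favourable stated power. No change to recruitment is needed: the Trial status section reports 78 of the 82 already enrolled. The correction should be made in writing before unblinding.
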